### Intervention manual

All CMs follow the guidance of a detailed intervention manual, thereby optimising consistency across all the sites. The work of CMs is overseen by an older persons’ mental health specialist (old age psychiatrist or psychologist). This is made possible by each CM being assigned a supervisor from the principle site (University of York) who has completed the IAPT Psychological Wellbeing Practitioner supervisor course.

### Usual care group

Participants allocated to the usual care group will receive usual primary care management of case level depression offered by their GP, including the prescription of any necessary medication. Participation in the trial will therefore not affect medication prescribing, which will remain entirely in the control of GPs.

### Case manager training

All CMs will participate in a comprehensive 3-day training programme delivered by supervisors at the University of York. This includes training on the use of the study specific manual, procedures, behavioural theories underpinning BA, medication management and specific training on working with older adults. This in-depth training aims to ensure adherence and fidelity to the model. We will not formally assess adherence and competence.

### Sample size calculation

In line with the IMPACT US trial [7] and the point estimate from our UK pilot trial [35], a standard effect size of 0.35 is sought as a conservative estimate of the detectable difference in mean PHQ-9 [36] depression severity scores between collaborative care and usual care. This difference equates to approximately 1.4 PHQ-9 score points (assumed SD = 4.1). In order to detect such a difference with 80% power at the 5% two-sided significance level, assuming an ICC of 0.02 (case load size of 20) and 20% loss to follow-up, the sample size needed will be 450 (225 in each group).

### Follow-up

Data collection will occur at six time points: at invitation, baseline (pre-randomisation/pre-assessment), diagnostic interview for participants entering the trial, at 4 months, 12 months and 18 months post randomisation/assessment. Additionally, primary care sources will be checked for medication prescribing during the participant’s time in the trial. Postal questionnaires will be used for data collection at baseline, 4-, 12- and 18-month follow-ups.

### Outcome measures

The primary outcome measure is mean depression severity at 4 months by self-report using the Patient Health Questionnaire 9 (PHQ-9) on a continuous scale. We will also measure outcome at 12 and 18 months using the PHQ-9 to examine any sustained impact of the intervention.

Secondary outcomes include the SF-12 [37] and GAD-7 [38] at 4, 12 and 18 months. We will also collect data on somatic symptom severity using the PHQ-15 [39], participant resilience using the CD-RISC2 and cost effectiveness including the EQ-5D [40], prescribed medication and health and social care use. Resource utilisation and cost data will be collected to fully reflect the management of depression and the consequential ‘total healthcare costs’ for individuals in both collaborative care and usual care groups, and these will be analysed within a societal perspective.

### Data analysis

#### Statistical analysis of clinical data

We will analyse the data on an ‘intention-to-treat’ basis. The primary outcome of depression severity is the continuous PHQ-9 depression score. Data will be analysed by a mixed effects model to compare collaborative care with usual care over all follow-up time points. The analysis will be adjusted for baseline depression severity (PHQ-9 score) and physical functional limitations (SF-12 physical component score). Estimates of the mean difference between randomised groups at 4 months follow-up will constitute the primary end point and will be presented with 95% confidence intervals. The analysis will include all patients with valid PHQ-9 scores at any follow-up time point and complete covariate data [30].

The number of non-responders will be calculated for each treatment group and response rates compared. We will undertake a secondary analysis to explore the impact of missing data by including predictors of non-response as covariates in the primary model. Analyses of secondary outcomes will be conducted using linear or logistic mixed models, depending on the outcome measure, adjusting for the same covariates as the primary analysis. Variability of within-therapist clustering will be explored by including CMs as random effects in the primary analysis. Full details will be provided in the statistical analysis plan.

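### The primary model excludes randomised patients who have a follow-up PHQ-9 but lack a baseline covariate: an avoidable, probably small loss of patients and precision under an intention-to-treat label

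*Protocol article*

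**What the plan says.** All of the relevant text is in the Protocol article, under Statistical analysis of clinical data.

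- Basis: "We will analyse the data on an ‘intention-to-treat’ basis".
- Covariates of the primary mixed model: "The analysis will be adjusted for baseline depression severity (PHQ-9 score) and physical functional limitations (SF-12 physical component score").
- Analysis set: "The analysis will include all patients with valid PHQ-9 scores at any follow-up time point and complete covariate data".
- Missing data: a secondary analysis will "explore the impact of missing data by including predictors of non-response as covariates in the primary model".

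Imputation of baseline values is not mentioned. Secondary outcomes are to be adjusted for the same covariates as the primary outcome. Full details are left to the statistical analysis plan, but the inclusion rule itself is already fixed here.

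Three other sections bear on the point. Follow-up says that baseline data are collected by postal questionnaire before randomisation. Identifying participants with major depressive disorder says that the diagnostic interview, and hence randomisation, follows receipt of a valid baseline questionnaire; it does not define valid. Inclusion criteria makes the PHQ-9 part of the eligibility assessment.

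**The concern.** The analysis set carries two conditions. The first, at least one valid follow-up PHQ-9, is a practical limit of a likelihood-based mixed model. The second, complete covariates, is not: it removes randomised patients whose outcome is known. That departs from the intention-to-treat basis stated in the same paragraph.

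The planned missing-data analysis does not recover these patients. It adds covariates to the same model, so under the same completeness rule it could drop more patients if the added predictors have gaps of their own. The secondary outcome models use the same two covariates and would meet the same problem.

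At stake are a number of randomised patients and some precision. The sample size makes no allowance for this loss: its 20% is for loss to follow-up only.

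**Working it through.** **Inputs.** From Sample size calculation: standardised effect 0.35; "with 80% power at the 5% two-sided significance level"; "assuming an ICC of 0.02 (case load size of 20) and 20% loss to follow-up"; 225 patients per arm. Not in the article, and so assumed: the share m of patients lacking a covariate (2%, 5%, 10%, missing completely at random) and the correlation ρ between the covariates and follow-up PHQ-9 (0, 0.3, 0.5).

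**Step 1: reproduce the plan's figure.**
- Per arm, n = 2 × (1.960 + 0.842)² / 0.35² = 128.1, so 129 (130 with the t distribution).
- Design effect = 1 + (20 − 1) × 0.02 = 1.38.
- Normal approximation: 129 × 1.38 / 0.8 = 222.5, so 223 per arm, 446 in total.
- t-test: 130 × 1.38 / 0.8 = 224.3, so 225 per arm, 450 in total.

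The stated 450 reproduces.

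**Step 2: power with no covariate missing.** With 225 × 0.8 = 180 per arm, the effective n is 180 / 1.38 = 130.4. Unadjusted power = Φ(0.35 × √(130.4/2) − 1.96) = Φ(0.867) = 80.7%.

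**Step 3: power with covariates missing.**
- Complete covariates only: effective n = 130.4 × (1 − m), residual variance 1 − ρ².
- Pooled mean imputation: effective n = 130.4, residual variance (1 − m)(1 − ρ²) + m.

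| m | Analysed at 4 months (of 360) | ρ = 0: complete / imputed | ρ = 0.3: complete / imputed | ρ = 0.5: complete / imputed |
|---|---|---|---|---|
| 2% | 353 | 79.9% / 80.7% | 83.5% / 84.1% | 89.8% / 90.2% |
| 5% | 342 | 78.7% / 80.7% | 82.3% / 84.0% | 88.9% / 89.9% |
| 10% | 324 | 76.5% / 80.7% | 80.3% / 83.9% | 87.2% / 89.5% |

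The difference in power is 0.4 to 0.8 points at 2% missing, 1.0 to 2.0 at 5%, and 2.2 to 4.2 at 10%.

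**Step 4: when does power fall below 80%?** The complete-covariate analysis has exactly 80% power when 0.35 × √(n/2) / √(1 − ρ²) = 2.802, where n is its effective size. The numerator is 2.798, 2.755 and 2.681 for m = 2%, 5% and 10%. Solving ρ = √(1 − (numerator / 2.802)²) gives about 0.05, 0.18 and 0.29. Power is below 80% only when the correlation is smaller than that.

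**Step 5: check by simulation.** With ρ = 0.5, a true effect of 0.35 and 10,000 runs per setting, power for complete covariates against mean imputation was 88.6% against 89.7% at 5% missing, and 87.7% against 89.6% at 10%. The mean treatment estimate was between 0.348 and 0.353 under both methods in every setting, so neither showed bias.

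These figures concern the 4-month comparison alone. They ignore whatever the repeated-measures model gains from later visits.

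**The case against.** The strongest objection is that the problem may hardly arise. Patients reach randomisation only after a valid baseline questionnaire, and the PHQ-9 is part of eligibility, so baseline PHQ-9 should rarely be missing. This stands and limits the size of the point. It does not remove it: valid is undefined, and nothing says that it requires a scorable SF-12 PCS. If it does guarantee both covariates, the completeness condition is redundant and can go.

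A reader might infer from the ρ = 0 column that the trial drops below its planned power. The article does not support that. The exclusion exists only because the model adjusts for covariates, and the same adjustment gains precision; at ρ = 0.3, power is still 80.3% with 10% missing. The formula also applies the design effect to both arms, although case managers treat only the intervention arm. With clustering in that arm alone, the variance is (1.38 + 1) / (180 × 0.9) at 10% missing, and power is 82.3% even at ρ = 0.

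A reader might also say that the intention-to-treat statement is false, or that the exclusion biases the comparison. Neither follows. The restriction is stated openly, nothing suggests that patients are analysed other than as randomised, and the remedy below still requires a follow-up PHQ-9. Baseline missingness precedes allocation and cannot depend on it. Nor do the secondary models worsen matters by adding covariates: the article says they use the same ones, and only the missing-data analysis adds more.

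Finally, item-level scoring rules properly belong to the analysis plan, which is not shown. That is fair for scoring, but the exclusion of patients with incomplete covariates is a choice that the article itself makes.

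**Conclusion.** The point holds in a limited form. As written, the rule discards randomised patients with known outcomes, departs from the stated intention-to-treat basis, and is not offset by any described analysis. The harm is lost patients and a modest loss of precision. On the assumed ranges, 7 to 36 of the 360 patients expected at 4 months would be excluded, at a cost of about 0.4 to 4.2 points of power. The true loss is probably towards the lower end if the baseline questionnaire check works, but the article gives no rate from which to judge. A shortfall below 80% power is conditional on covariates that predict outcome weakly or not at all; it is not a finding. The change is worth making because it costs almost nothing.

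**What to change.** In the analysis-set sentence, delete the requirement for complete covariates and substitute: *missing baseline PHQ-9 or SF-12 PCS is replaced by the pooled baseline mean across both arms, without using outcome.* Every randomised patient with any follow-up PHQ-9 then enters the primary model. Keep the complete-covariate analysis as a sensitivity check.

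Single mean imputation is acceptable here because the covariates are measured before randomisation and the filled-in value depends on neither arm nor outcome.

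Cost: one sentence in the analysis plan and trivial programming. The one statistical downside is slightly less covariate adjustment for the patients whose value is imputed; the imputed columns of the table already include it.

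### The covariate rule for secondary outcomes omits the own baseline of the SF-12 mental component, and of GAD-7, PHQ-15 and CD-RISC2 if measured at baseline: a minor loss of precision

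*Protocol article*

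**What the plan says.** All places are in the protocol article.

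- Statistical analysis of clinical data: the primary analysis is "adjusted for baseline depression severity (PHQ-9 score) and physical functional limitations (SF-12 physical component score"). On the model type for the other outcomes it says: "Analyses of secondary outcomes will be conducted using linear or logistic mixed models, depending on the outcome measure". The covariate rule that it attaches to these models is "adjusting for the same covariates as the primary analysis". The subsection closes with "Full details will be provided in the statistical analysis plan".
- Outcome measures: "Secondary outcomes include the SF-12 [37] and GAD-7 [38] at 4, 12 and 18 months". It adds "We will also collect data on somatic symptom severity using the PHQ-15 [39], participant resilience using the CD-RISC2", with no time points for these two scales. For the primary scale, "We will also measure outcome at 12 and 18 months using the PHQ-9".
- Follow-up: "Postal questionnaires will be used for data collection at baseline, 4-, 12- and 18-month follow-ups". The scales in the baseline questionnaire are not listed.

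**The concern.** The sentence on secondary outcomes is a positive rule, not a gap: it fixes the covariate set. That set suits PHQ-9, because it contains PHQ-9's own baseline. Carried over unchanged, it gives GAD-7 a baseline depression score but no baseline anxiety score, and gives the SF-12 mental component the baseline of the other half of the same instrument.

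A scale's own baseline is usually its strongest single predictor. Leaving it out raises the residual variance and widens the confidence interval. It also leaves any chance difference between groups in that baseline uncorrected, except for the part shared with PHQ-9 and the physical score. At stake is how sharply the trial can speak on anxiety, mental quality of life, somatic symptoms and resilience. The primary result is not at stake.

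**Working it through.** **1. Which outcomes are affected.**

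| Outcome | Own baseline in the stated covariates? | Baseline collection shown in the article? |
|---|---|---|
| PHQ-9 at 12 and 18 months | Yes | Yes |
| SF-12 physical component | Yes | Yes, as it is a covariate |
| SF-12 mental component | No | Yes by implication: same instrument |
| GAD-7 | No | Not stated |
| PHQ-15, CD-RISC2 | No | Not stated |

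**2. The plan's own figure.** The Sample size calculation section gives 450 for PHQ-9: effect size 0.35, 80% power, two-sided 5%, ICC 0.02, case load 20, 20% loss. This needs 129 per group. The design effect is 1 + 19 × 0.02 = 1.38, so 129 × 1.38 gives 179; 179 / 0.8 gives 224; the total is 448. The stated figure therefore reproduces. The article gives no precision figure for secondary outcomes.

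**3. Precision formula (continuous outcome, one time point).** Assumed inputs, none of them in the article:
- r: correlation of an outcome's own baseline with its follow-up value, 0.4 to 0.6
- p: correlation of that baseline with baseline PHQ-9, 0.3 to 0.7
- baseline PHQ-9 predicts follow-up only through the own baseline, so its correlation with follow-up is p × r
- the SF-12 physical score is ignored

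Residual variance as written is 1 − (p r)². With the own baseline added it is 1 − r². The variance ratio is (1 − r²) / (1 − (p r)²), and the interval width scales with its square root.

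| r | p | Variance ratio | Interval narrower by |
|---|---|---|---|
| 0.4 | 0.7 | 0.84 / 0.9216 = 0.911 | 4.5% |
| 0.4 | 0.5 | 0.84 / 0.96 = 0.875 | 6.5% |
| 0.5 | 0.4 | 0.75 / 0.96 = 0.781 | 11.6% |
| 0.6 | 0.5 | 0.64 / 0.91 = 0.703 | 16.1% |
| 0.6 | 0.3 | 0.64 / 0.9676 = 0.661 | 18.7% |

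**4. Relaxing the third assumption.** Take r = 0.4 and p = 0.5, and let baseline PHQ-9 correlate 0.35 directly with follow-up. With both covariates, R² = (0.16 + 0.1225 − 2 × 0.4 × 0.35 × 0.5) / (1 − 0.25) = 0.1425 / 0.75 = 0.19. The ratio is 0.81 / (1 − 0.1225) = 0.81 / 0.8775 = 0.923, so the interval is about 4% narrower.

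**5. What this means for power (r = 0.6, p = 0.5).** The effective number per group, using the plan's loss and design effect, is 225 × 0.8 / 1.38 = 130. The standard error is √(0.91 × 2 / 130) = 0.118 SD as written and √(0.64 × 2 / 130) = 0.099 SD with the own baseline. The difference detectable with 80% power is 0.33 SD against 0.28 SD. Power for 0.25 SD is 56% against 71%.

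**6. Validity.** A simulation of 4,000 trials with no treatment effect (r = 0.6, p = 0.5, 180 per group, no clustering) gave a mean estimate of 0.002 under both covariate sets. Type I error was 0.050 as written and 0.055 with the own baseline. The SD of the estimate fell from 0.101 to 0.086.

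**7. Chance imbalance.** If the groups differ by 0.1 SD in the own baseline while PHQ-9 is balanced, the estimate as written shifts by 0.1 × r, that is 0.04 to 0.06 SD.

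**The case against.** **The detail is left to the SAP.** The SAP is not shown and may add own baselines. The phrase could also be shorthand for a structure: the outcome's own baseline plus physical function. Both are possible. But the published sentence names a covariate set, and an SAP that adds own baselines would depart from it. The wording is worth correcting either way.

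**Baselines may not exist.** Outcome measures schedules SF-12 and GAD-7 at 4, 12 and 18 months and gives PHQ-15 and CD-RISC2 no schedule. This stands: of the affected outcomes, only the SF-12 mental component has a baseline that the article supports. The others depend on what the baseline questionnaire contains.

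**The gain may be small.** This also stands. It rests on assumed correlations, and plausible inputs bring it down to about 4%. The variance formula does not carry over to logistic models, where adding a prognostic covariate changes the conditional odds ratio and generally does not narrow its interval.

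**Extra covariates can cost participants.** The primary analysis is limited to participants with complete covariates. If that rule carries over, each added baseline could exclude people, so the fix has to deal with this.

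**Stronger readings that the article does not support.** A reader might infer that every secondary comparison is affected; the table in the working shows two that are not. A reader might infer bias; under randomisation a chance imbalance is ordinary sampling error already covered by the confidence interval, and the simulation agrees. A reader might extend the point to the QALY analysis; the Analysis of economic data section states no covariates, so nothing there is wrong on this point.

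**Conclusion.** The point holds as a minor improvement to the secondary analyses. As worded, the rule leaves out the own baseline of the SF-12 mental component, and of GAD-7, PHQ-15 and CD-RISC2 if these are collected at baseline. The consequence is avoidable imprecision, not bias or an inflated error rate. Under the assumed correlations (0.4 to 0.6 with follow-up, 0.3 to 0.7 with baseline PHQ-9), the interval for a continuous outcome would be roughly 4% to 19% narrower with the own baseline. The direction is dependable wherever the own baseline predicts follow-up beyond the covariates already in the model. The size is not known from the article.

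**What to change.** Extend the sentence so that it reads: "adjusting for the same covariates as the primary analysis" and, where collected, the baseline value of the outcome itself. Outcomes with no baseline measure keep the present covariates.

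Also state how missing baseline covariates are handled, for example by simple imputation, so that the added covariate does not remove participants from the analysis.

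The cost is one clause in the protocol and matching text in the SAP. No new data are needed for the SF-12 mental component or for any scale already in the baseline questionnaire. Because the trial is un-blinded, the change should be recorded before outcome data are examined by group.

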#### Analysis of economic data

Economic evaluation will take the form of within-trial cost-utility analysis to determine the incremental cost per quality adjusted life year (QALY) for treatment with collaborative care against usual care in individuals with depression. Following NICE evaluation guidelines, the primary analyses will be conducted from the perspective of the UK NHS and personal and social services (PPS). The cost-effectiveness acceptability curve (CEAC) will represent the probability that collaborative care is cost-effective compared to usual care for a range of maximum monetary values (ceiling ratios) that a UK decision-maker may be willing to pay for an increase in one unit of QALY. Furthermore, a net benefit analysis will be undertaken to evaluate the net monetary gain that can be achieved with implementation of collaborative care thus indicating to decision makers the value of the intervention in terms of monetary gain.

### Process evaluation

While a considerable evidence base exists for the role of collaborative care in improving treatment of depression in the USA, there is a recognised gap between demonstrated efficacy in trials and implementation in everyday practice, with particular uncertainty around whether the model will effectively translate to UK healthcare systems. The UK Medical Research Council has highlighted the need for process evaluations to understand the problems of integrating interventions into healthcare settings. A recent trial of collaborative care in the adult population [41] highlighted organisational barriers to embedding the intervention into routine primary care. The process evaluation for CASPER Plus will add to the existing literature by including data collection from patients, as well as identifying barriers and facilitators to implementation of this model of care in the older population, who view ‘depression’ very differently from the younger adult population [4].

We will therefore undertake a qualitative process evaluation to evaluate the extent to which the collaborative care model was delivered and received, and how it impacted on practices. The aims of the process evaluation are to explore:Feasibility and acceptability of the collaborative care intervention as experienced by both patients and professionals (CMs and GPs).Likely sustainability of collaborative care models of care beyond the trial.

The COREQ checklist, consolidated criteria for reporting qualitative research, is given in Table 3.

Clarity of minor themes	We will present minor themes and dis-confirmatory evidence in our outputs, particularly in report to HTA

### Data collection

Interviews will be conducted by a qualitative researcher with all CMs, a sample of trial participants including those who declined the intervention or dropped out, and a sample of GPs. The interviews will be digitally-recorded (with participant’s consent) and transcribed, and transcripts will form the data to be analysed initially thematically, using a constant comparison approach. The topic guide will be modified as data collection and analysis progresses. Data analysis will involve a process of organising the data, descriptive coding, interpretive coding, writing and theorising.

Comparative analysis both within and across the data sets will be carried out to allow data from different participants to be compared and contrasted. Deviant cases will be actively sought throughout the analysis and emerging ideas and themes modified in response. Data analysis will involve at least two members of the research team to independently read transcripts and discuss coding and emerging themes, supervised by [name]. We will then reanalyse the data using the framework of the Normalisation Process Theory [42] in order to explore the barriers and facilitators of incorporating this intervention into routine care.

The process evaluation is an integral component of CASPER Plus [43] and will add value to the trial in explaining the findings and increasing the utility of the trial results and implications for clinical practice.

